#### Descriptive analyses

The numbers of participants screened, excluded, randomly assigned to each group, interviewed at each follow-up, and analyzed will be summarized using a flow diagram recommended by CONSORT [27] (Fig. 2). Reasons for the losses to follow-up and withdrawals will also be listed by treatment arm.

**Fig. 2 Fig2:**
[figure not shown]
Flow diagram. EA electro-acupuncture, MA manual acupuncture, SA sham acupuncture

The demographic characteristics and clinical outcomes at baseline are those presented in Table 1. Missing data for baseline characteristics will not be imputed. Differences among the treatment groups at baseline will not be statistically tested.

**Table 1 Tab1:** Baseline characteristics

Baseline characteristic	Type	Levels or scale
Gender	Categorical	Male or female
Age	Continuous	Years
Nationality	Categorical	Han or other
Duration of disease	Continuous	Years
Kellgren–Lawrence grade	Categorical	Grade II or III
Body mass index	Continuous	kg/m^2^
Years of education	Categorical	<9, 9–12, or >12
Affected knee	Categorical	Unilateral or bilateral
Previous treatments	Categorical	Injections, medication, physical therapy, acupuncture, exercise, etc.
Concomitant diseases	Categorical	Hypertension, coronary heart disease, diabetes mellitus, hyperlipidemia, etc.
Numerical rating scale	Continuous	Point
WOMAC pain subscale	Continuous	Point
WOMAC function subscale	Continuous	Point
WOMAC stiffness subscale	Continuous	Point
Physical health, SF-12	Continuous	Point
Mental health, SF-12	Continuous	Point

*WOMAC* Western Ontario and McMaster Universities osteoarthritis index, *SF-12* 12-item Short Form Health Survey

#### Analysis of the primary outcome

In the analysis of the primary outcome, the response rates of the three groups at 8 weeks will be calculated and the *Z*-test for comparisons of proportions will be used with the full analysis set. Any missing data at 8 weeks will be imputed using the baseline value. There will be two comparisons. The first comparison is that between the EA group and the SA group. The second is that between the MA group and the SA group. The significance level will be adjusted at 0.025 for multiple comparisons using the Bonferroni method.

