### Outcomes

#### Primary outcome

The primary outcome is the response rate [20], which is the proportion of patients who achieve the minimal clinically important improvement in pain and function at 8 weeks post-randomization. The average pain over the previous week will be assessed using an 11-point numerical rating scale (NRS) [21] with scores ranging from 0 to 10. The minimal clinically important improvement in pain is defined as 2 points in the NRS [11, 22]. The average function over the previous week is measured using the Western Ontario and McMaster Universities Osteoarthritis Index (WOMAC) function subscale [23] with scores ranging from 0 to 68. The minimal clinically important improvement in function is defined as 6 points in the WOMAC function subscale [11, 22]. The criteria for a participant to be a responder are presented in Fig. 1. The response rate is also measured at weeks 4, 16, and 26 after randomization.

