### Sample size

Based on the results of our previous trial [16], the response rates for the EA, MA, and SA groups were assumed to be 70%, 60%, and 40%, respectively. With a two-sided significance level of 2.5% and power of 80%, 128 participants in each group will be required to detect a difference as small as 20% between each acupuncture group and the control group. The two-sided significance level of 2.5% is a Bonferroni-adjusted alpha level as per the two predefined primary comparisons: EA vs. SA and MA vs. SA. With an estimated loss-to-follow-up rate of 20%, 480 participants will be recruited in total.

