#### Analysis of secondary outcomes

For the NRS score, comparisons among the three groups will be assessed by a mixed-effect model with repeated measurement (MMRM) analysis using the NRS score at all follow-up time points as the dependent variable, treatment as the main factor, and the baseline value as a covariate. We set the model as

*y*_*ij*_ = *α* + *u*_*i*_ + *β*_1_time_*ij*_ + *β*_2_treat_*i*_ + *ε*_*ij*_

where *α* is the overall average and *u*_*i*_ is an unknown random effect represented as a subject-specified effect. *β*_1_ and *β*_2_ are unknown fixed effects represented as time and treatment effects, respectively. The covariance matrix *G* is unstructured, and *u*_*i*_~*N*(0, *G*). The random error *ε*_*ij*_~*N*(0, *R*_*i*_). The MMRM for secondary outcomes will be handled by PROC MIXED (SAS). The estimators of unknown parameters will be calculated using an expectation maximalization algorithm, which we expect will converge for the 480 participants in three groups and a single random intercept. If non-convergence does happen, we will consider correcting the initial value, changing the random effect, or using another analysis method like generalized estimating equations. Also, we will test the estimators or models based on a likelihood test and Bayesian information criterion methods.

The modified MMRM also has the center effect and time × treatment effect and it will be used in the sensitivity analysis. The modified MMRM is as follows:$$ {y}_{ij}=\upalpha +{u}_i+{\upbeta}_1{\mathrm{time}}_{ij}+{\upbeta}_2{\mathrm{treat}}_i+{\upbeta}_3{\mathrm{time}}_{ij}\times {\mathrm{treat}}_i+{\upbeta}_4{\mathrm{center}}_i+{\upvarepsilon}_{ij} $$

where α, u_*i*_, β_1_, β_2_, and ε_*ij*_ are defined as above. β_3_ and β_4_ are unknown fixed effects.

The same approach will be used to analyze the pain, function, and stiffness WOMAC subscales, and SF-12. If normality is violated in the continuous variables, a transformation will be performed before the comparison. A chi-square test will be used for the patient global assessment. These outcomes are shown in Table 2.

**Table 2 Tab2:** Primary and secondary outcomes

Outcomes	EA (*n*)	MA (*n*)	SAb (*n*)	*P* value	Pairwise comparison					
					EA vs. SA		MA vs. SA		EA vs. MA	
					Difference (95% CI)	*P* value	Difference (95% CI)	*P* value	Difference (95% CI)	*P* value
Success rate, no. (%)										
4 weeks	x (xx.x)	x (xx.x)	x (xx.x)	–	xx.x (xx.x- xx.x)	xx.x	xx.x (xx.x- xx.x)	xx.x	–	–

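### The primary Z-test is valid and adequately powered, but it leaves out baseline NRS and WOMAC function, giving up some precision that matters in practice only for MA vs SA

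*SAP article*

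**What the plan says.** The section Analysis of the primary outcome fixes the confirmatory method as follows: "the response rates of the three groups at 8 weeks will be calculated and the *Z*-test for comparisons of proportions will be used". No covariate is named, each of the two comparisons is tested at 0.025, and a missing week-8 value is replaced by the baseline value.

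Under Primary outcome, response rests on an improvement of 2 points on the 0–10 NRS and on a function threshold: "The minimal clinically important improvement in function is defined as 6 points in the WOMAC function subscale". The detailed criteria are in Fig. 1, which is not shown. Table 1 lists NRS and WOMAC function as continuous baseline characteristics.

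For the NRS score as a secondary outcome, the text specifies "treatment as the main factor, and the baseline value as a covariate" (the printed model equation has no such term). The same approach applies to the WOMAC subscales and SF-12. Additional analyses lists three other ways of handling missing primary data and a Kellgren–Lawrence subgroup analysis. None is described as adjusting the treatment comparison for baseline pain or function.

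**The concern.** Whether a patient improves by a fixed number of points depends partly on the starting score: someone who starts low has less room to gain 2 NRS points or 6 function points. The two baseline scores are therefore likely to predict response. A test that ignores a prognostic baseline variable carries variance that could be removed at no cost in patients or data.

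The plan accepts this reasoning for supportive outcomes but does not apply it to the outcome on which its conclusions rest. At stake is the chance of missing a real MA effect, since MA vs SA has the smaller assumed difference.

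**Working it through.** **Inputs from the document (Sample size).** "the response rates for the EA, MA, and SA groups were assumed to be 70%, 60%, and 40%, respectively"; 80% power and 128 per group at a two-sided 2.5% level; 20% loss; 480 in total. Two-sided 0.025 gives z = 2.2414, and 80% power gives z = 0.8416.

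**Inputs not in the document (assumed).** Baseline means and SDs, the correlation between baseline and week 8, and the responder rule. Both thresholds are taken as required because Fig. 1 is not shown.

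**1. The plan's own figure.** For 60% vs 40%:

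n = [2.2414·√(2·0.5·0.5) + 0.8416·√(0.24+0.24)]² / 0.2² = (1.5849 + 0.5831)² / 0.04 = 117.5, so 118 per group.

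Continuity correction: (117.5/4)·[1 + √(1 + 4/(117.5·0.2))]² = 127.3, so 128. Then 128/0.8 = 160 per group and 3 × 160 = 480. Both stated figures reproduce.

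**2. Power of the planned test at 128 per group.**

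- MA vs SA: Φ[(0.2·√128 − 1.5849)/0.6928] = Φ(0.978) = 83.6%.
- EA vs SA (70% vs 40%): Φ[(0.3·√128 − 2.2414·√0.495)/√0.45] = Φ(2.709) = 99.7%.

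**3. Adjustment by formula.** If baseline explains a share R² of response variance, the effective n is n/(1 − R²). For R² = 0.10, n = 142.2 and MA vs SA power is Φ[(0.2·√142.2 − 1.5849)/0.6928] = 87.6%. For R² = 0.02, 0.05 and 0.20 it is 84.4%, 85.6% and 91.4%. EA vs SA moves from 99.66% to at most 99.95%.

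**4. Adjustment by simulation, MA vs SA, 128 per group.** NRS and function are simulated as rounded, bounded scores with a pain–function correlation of 0.5 (sets A and B), and arms are calibrated to 60% and 40%.

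- Set A: baseline NRS 6 (SD 1.7), function 26 (SD 11); standardised logistic model; 3,000 trials.
- Set B: NRS 5.5 (SD 1.5), function 25 (SD 11), follow-up SDs 2 and 12; linear model with robust standard error; 4,000 trials.
- Set C: baseline means and SDs as in B; standardised logistic model; 4,000 trials.

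| Correlation, baseline to week 8 | Set A | Set B | Set C |
|---|---|---|---|
| 0.3 | 85.3 → 92.5% (+7.2) | 83.7 → 88.7% (+5.0) | 84.8 → 90.6% (+5.8) |
| 0.5 | 85.3 → 90.4% (+5.1) | 83.9 → 85.9% (+2.0) | 84.6 → 87.6% (+3.0) |
| 0.7 | 84.4 → 87.2% (+2.8) | 85.5 → 85.8% (+0.3) | 85.9 → 86.3% (+0.4) |

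The gain falls as the correlation rises because the outcome is a change. The slope of improvement on baseline is 1 − ρ·(follow-up SD/baseline SD). For NRS in set B this is 1 − 0.3·1.33 = 0.60 at ρ = 0.3, but 1 − 0.7·1.33 = 0.07 at ρ = 0.7. Baseline explained about 22%, 16% and 11% of response variance in set A, and about 14%, 8% and 3% in the SA arm of set B. For EA vs SA, set B gains were 0.3 points or less.

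**5. With missing data counted as non-response.** If 20% of 160 per group are missing and take their baseline value, 60/40 becomes 48/32. Unadjusted power is Φ[(0.16·√160 − 2.2414·√0.48)/√0.4672] = Φ(0.689) = 75.5%. Adjustment adds 6.3, 5.2 and 2.9 points in set A and 5.3, 3.8 and 0.9 in set C (correlations 0.3, 0.5, 0.7).

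**6. Type I error of the adjusted test (nominal 0.025).** Set A, 4,000 null trials: 0.028–0.033, against 0.024–0.029 unadjusted (Monte Carlo SE about 0.0025). Set C with a degrees-of-freedom correction, 8,000 null trials: 0.025–0.028, against 0.023–0.026 unadjusted.

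None of these adjusted models included center.

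**The case against.** The strongest case for the plan is that nothing in it is incorrect. Under 1:1:1 randomisation the two-proportion Z-test is valid, matches the two stated hypotheses, and is the kind of comparison the trial was sized on. Its planned power is met. All of this stands, and it makes the point one of efficiency.

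It is also fair that the gain rests on unseen inputs. Eligibility is left to the protocol, and a minimum-pain criterion would narrow the baseline range. With an assumed floor of NRS 4, explained variance fell from 21/15/10% to 18/13/8% at the three correlations. This limits the size claimed, not the direction: no simulated setting showed a loss of power.

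Four stronger readings are tempting and are not supported:

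- **That power is lost in both comparisons.** Precision is given up in both, but EA vs SA stands at 99.7% on the plan's own rates, so nothing of practical weight is lost there.
- **That the result is biased because a chance baseline imbalance feeds into it.** Such imbalance is already covered by the test's type I error.
- **That a correlation of 0.5 gives a 25% variance reduction.** That squared-correlation rule concerns a continuous follow-up value. For this dichotomised change, the simulations gave about 16% and 8% explained variance at 0.5.
- **That the 75.5% in step 5 shows the Z-test to be underpowered.** It comes from counting missing patients as non-responders, a separate matter that adjustment does not remove. It is also a worst case, because patients with no post-baseline measurement leave the modified full analysis set. With 10% missing (54% vs 36% at 160 per group), power is 84.4%.

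**Conclusion.** The concern holds as a modest, avoidable loss of precision. The primary test ignores two baseline scores from which its own outcome is derived, and no adjusted analysis of response is planned. For MA vs SA the power given up is about 0 to 7 points: near the top when baseline and week 8 are weakly correlated (0.3), near zero at 0.7 under two of the three sets of assumptions. For EA vs SA it is negligible. These figures rest on assumed baseline distributions, assumed correlations, and a responder rule requiring both thresholds. The change is worth making because it is cheap; the planned analysis would still be valid without it.

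**What to change.** Under Analysis of the primary outcome, keep the difference in week-8 response rates, the two comparisons and the 0.025 level. Replace the test with the following:

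- Fit a logistic regression of response on treatment, continuous baseline NRS, continuous baseline WOMAC function and center (the randomisation stratum).
- Standardise the predicted probabilities to an adjusted risk difference for EA vs SA and MA vs SA.
- Test each with a robust standard error corrected for degrees of freedom, since the uncorrected version ran slightly above nominal.
- Report the unadjusted Z-test as a supporting analysis.

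No new data or patients are needed. The costs are an amendment to a plan approved on 30 October 2017 and two estimates to tabulate. All 480 patients were randomised by October 2018, but the article says it was written before data collection ended and without knowledge of the data. The amendment should be dated and signed off before unblinding.

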## Methods/design

### Study design

This three-arm randomized sham-controlled trial has been approved by the ethics committees at each of the nine participating hospitals. Eligible KOA participants, diagnosed according to the American College of Rheumatology criteria [19], are randomly assigned (1:1:1) to receive 24 sessions of EA, MA, or SA over 8 weeks. The block randomization, with block sizes of 6 and 9, is stratified by study center and is performed via a web-based randomization system. Superficial insertion at non-acupoints with no electric current will be used for the SA group, which is one of the most commonly used approaches for administering sham treatments in acupuncture trials. The nature of acupuncture means that acupuncturists are not blinded to treatment allocation; however, patients, outcome assessors, and statisticians will remain masked. Informed consent will be obtained from each participant before randomization. The trial has been registered with ClinicalTrials.gov (NCT03366363).

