## Discussion and trial status

The trial will provide high-quality evidence of the efficacy of EA and MA for KOA. This paper provides details of the planned statistical analyses for the current trial and will help to reduce the risks of outcome reporting bias and data-driven results [29]. This paper has been prepared in accordance with the published guidelines for the content of statistical analysis plans [30]. As of October 2018, 480 patients from nine centers had been randomized. The final date of follow-up is April 7, 2019. This analysis plan was written prior to completion of the trial data collection phase.

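### Randomisation is stratified by centre, but the primary Z-test and the main MMRM leave centre out, so the stated precision is conservative if centres differ

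*SAP article*

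**What the plan says.** Under Study design, allocation is 1:1:1 and "The block randomization, with block sizes of 6 and 9, is stratified by study center". Discussion and trial status records that "480 patients from nine centers had been randomized".

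Under Analysis of the primary outcome, the 8-week response rate is compared for EA versus SA and for MA versus SA, each at 0.025. The Z-test "for comparisons of proportions will be used with the full analysis set". No stratification or covariate is named.

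Additional analyses lists three other ways of handling missing 8-week data and a subgroup analysis by Kellgren–Lawrence grade. Centre appears in none of them, and it is not among the predictors for the multiple imputation.

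Under Analysis of secondary outcomes, the main MMRM equation contains time and treatment, with the baseline value named in the text. Centre comes in only afterwards: "The modified MMRM also has the center effect", and that version is reserved for sensitivity analysis.

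**The concern.** Blocked randomisation within centre makes the arms nearly equal in size at every centre. Differences between centres in the overall response rate therefore largely cancel out of the comparison between arms. The pooled Z-test does not use this: its variance treats all patients in an arm as draws from one common proportion, so between-centre variation is counted as noise. The test then rejects less often than its nominal level under the null, the confidence interval is wider than it needs to be, and part of the precision gained by stratifying is not used.

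General analysis principles rests the trial's conclusions on the primary outcome. Yet the only centre-adjusted analysis in the article concerns the secondary outcomes. The authors considered centre and applied it where the conclusions do not rest.

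**Working it through.** **Inputs from the article.** Nine centres, 480 patients, 1:1:1. Under Sample size, "the response rates for the EA, MA, and SA groups were assumed to be 70%, 60%, and 40%, respectively", and "With a two-sided significance level of 2.5% and power of 80%, 128 participants in each group will be required"; loss to follow-up is 20%.

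**Reproducing the sample size (60% versus 40%).** With p̄ = 0.5, z(0.9875) = 2.2414 and z(0.80) = 0.8416:

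n = [2.2414·√(2·0.5·0.5) + 0.8416·√(0.24 + 0.24)]² / 0.20² = (1.5849 + 0.5831)² / 0.04 = 117.5, so 118 per group.

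With the continuity correction: (117.5/4)·[1 + √(1 + 4/(117.5·0.20))]² = 127.3, so 128. Then 128/0.80 = 160 per arm, and 3 × 160 = 480. The article's figures reproduce.

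**Why the standard error is too large.** With n per arm, equal numbers in both arms at each centre, and a common response rate p_k at centre k under the null:

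- variance used by the Z-test: (2/n)·p̄(1 − p̄)
- actual variance of the difference: (2/n)·[p̄(1 − p̄) − σ²], where σ² is the between-centre variance of the response rate.

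Example with p̄ = 0.40, n = 160 and σ = 0.134 (about 13 points). The Z-test uses √(0.0125 × 0.24) = 0.0548. The actual value is √(0.0125 × (0.24 − 0.0180)) = 0.0527. Averaged over simulated trials, the estimated and actual standard errors at 160 per arm are:

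- logit SD 0.4: 0.0546 and 0.0538, overstated by about 1.5%
- logit SD 0.6: 0.0544 and 0.0527, about 3%
- logit SD 1.0: 0.0542 and 0.0499, about 9%

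**Effect on type I error and power.** The article gives no between-centre variance, so it is an assumption shown as a range. The settings are nine equal centres (480/9/3 = 17.8, taken as 18 per arm per centre, 162 per arm), normal centre effects on the logit scale with overall rates held at target, no treatment-by-centre interaction, and 60,000 runs. The rejection rule is |z| > 2.241. CMH uses Σ(a_k − m_k/2)/√ΣV_k, where a_k is the number of responders in the active arm at centre k, m_k the responders in both arms, n_k the patients per arm, N_k = 2n_k, and V_k = n_k²·m_k(N_k − m_k)/[N_k²(N_k − 1)].

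Two pairs of rates are shown: the article's 60% versus 40%, and 0.8 × these, 48% versus 32%. The second is the case in which the full 20% loss is equal across arms, stays in the analysis set and, through baseline imputation, counts as non-response.

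| Logit SD between centres | SD in points around 40% | Type I error, Z / CMH | Power 60% v 40%, Z / CMH | Power 48% v 32%, Z / CMH |
|---|---|---|---|---|
| 0 | 0 | 2.5% / 2.5% | 91% / 91% | 77% / 76% |
| 0.4 | about 9 | 2.4% / 2.5% | 92% / 93% | 77% / 78% |
| 0.6 | about 13 | 2.0% / 2.5% | 92% / 93.5% | 77% / 79% |
| 0.8 | about 17 | 1.8% / 2.5% | 93% / 95% | 78% / 81% |
| 1.0 | about 20 | 1.5% / 2.5% | 93% / 96% | 78% / 83–84% |

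For EA versus SA at 70% versus 40%, power exceeds 99.9% for both tests at every spread.

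**MMRM.** Omitting centre inflates the standard error of the treatment effect by about 1/√(1 − ρ), where ρ is centre's share of the between-subject variance. With ρ assumed to be 0.01, 0.05 and 0.10, the inflation is 0.5%, 2.6% and 5.4%.

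**The case against.** The strongest reply is that this concerns efficiency and not validity. The sample size and the primary test are coherent with each other, the error is conservative, and at the plan's own rates both comparisons stay above 90% power. The gain rests on a variance that nobody has stated, and at small spreads it is a point or less. The continuous secondary outcomes already have a centre-adjusted sensitivity model, and they only support the primary analysis. All of this stands, and it sets the weight of the point.

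The reply does not remove the omission. No stated analysis of the primary outcome uses centre, and with no centre variation CMH costs essentially nothing (91% against 91%, or 76% against 77%). Nor is this merely an article being brief, because the article names the primary test and writes out a centre term for another model.

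Three stronger readings are tempting, and the article supports none of them.

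- A reader might infer that ignoring centre leaves the trial underpowered. Z-test power does not fall as centres diverge: it moves from 91% to 93%, or from 77% to 78%. The figure below 80% in the 48% versus 32% column comes from counting all losses as non-responders. That column is also an extreme case, since Statistical analysis population excludes patients with no post-baseline measurement.
- A reader might infer that a positive result would be suspect. The type I error lies at or below nominal, so it would not be.
- A reader might extend the argument to baseline NRS and WOMAC function. These were not stratification factors. Adjusting for them is an optional gain in efficiency and not part of this point.

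**Conclusion.** The point holds as a matter of efficiency. Centre governs the randomisation but is absent from the primary test, from every further analysis of the primary outcome and from the main MMRM. If centres differ, the Z-test's type I error falls below 0.025, to about 1.5% at the widest spread tried. The power forgone is about 0 to 3 points at 60% versus 40%, and from nil to about 5 or 6 points if the whole planned loss counts as non-response. If centres do not differ, nothing is lost.

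These sizes assume equal centres, normal centre effects on the logit scale, no treatment-by-centre interaction and exact balance within centre. The omission and the direction of its effect are certain; the size is not. The sample size of 480 stands.

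**What to change.** For each of the two primary comparisons, make the primary test a CMH test stratified by centre at 0.025, and report the Mantel–Haenszel risk difference with its confidence interval. Use the same stratified test under the three alternative missing-data schemes. Keep the unstratified Z-test as a sensitivity analysis. Move the centre term already written in the modified MMRM into the main MMRM.

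The cost is a few lines of SAP wording and a standard stratified-table procedure in SAS, which the plan already uses. Centre is already recorded because it drives the randomisation, so no new data are needed and the sample size does not change. The amendment should be dated before unblinding. Adjustment for baseline NRS and WOMAC function may be added as a supplementary analysis if wanted.

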### Statistical analysis

#### Statistical analysis population

A modified full analysis set, a per-protocol set, and a safety set will be used in this trial. The modified full analysis set will consist of all randomized participants who have at least one post-baseline measurement according to the modified intention-to-treat principle. The modified full analysis set will be the primary analysis set, and all analyses will be conducted for this population if not otherwise stated. Analyses of the modified full analysis set will provide an estimate of the effects of EA and MA.

The per-protocol set will include those who complete the treatment and follow-up on time according to the protocol without major violations. Major violations of the protocol will be judged during the blinded audit of the data. They include but are not limited to not meeting the inclusion criteria, meeting the exclusion criteria, receiving other treatments that might affect the symptoms of KOA during the trial, and completing <20 sessions of acupuncture. The per-protocol set will be the secondary analysis set and will be used for the sensitivity analyses.

All those who are randomized and have received at least one session of acupuncture will be defined as the safety set, which is used for the safety analyses.

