#### Additional analyses

Another three schemes to deal with any missing data for the primary outcome will be carried out to examine the robustness of the conclusion. First, any data missing at 8 weeks will be imputed using the last observation carried forward approach. Second, we will directly remove any missing data. Third, any data missing at 8 weeks will be imputed using multiple imputation [28]. By assuming the data missing are random, the missing data will be imputed using the Monte Carlo Markov chain method for multiple imputation with Proc MI (SAS). The initial seed will be set at 1000 and five datasets will be imputed. Any data missing for the primary outcome will be imputed by the observation value of age, gender, body mass index, Kellgren–Lawrence grade, and duration of disease. A subgroup analysis based on Kellgren–Lawrence grade will be performed.

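### Baseline imputation counts patients with missing week-8 scores as non-responders, and the planned checks do not cover drop-out that depends on outcome differently by arm

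*SAP article*

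**What the plan says.** The section on analysis of the primary outcome compares 8-week response rates by Z-test, EA vs SA and MA vs SA, each at 0.025, and adds: "Any missing data at 8 weeks will be imputed using the baseline value". The outcomes section sets the improvements needed at 2 NRS points and 6 WOMAC function points.

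The section on the analysis population limits who is covered: "The modified full analysis set will consist of all randomized participants who have at least one post-baseline measurement". Patients without such a measurement are not in the primary set and so are not imputed.

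The additional analyses section continues: "Another three schemes to deal with any missing data for the primary outcome will be carried out". These are last observation carried forward, deletion, and multiple imputation under missing at random. The imputation model lists age, gender, body mass index, Kellgren–Lawrence grade and duration of disease.

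The sample size section plans on response in 70% of EA, 60% of MA and 40% of SA patients. The group size follows from the smaller contrast: "With a two-sided significance level of 2.5% and power of 80%, 128 participants in each group will be required". Losses are then allowed for: "With an estimated loss-to-follow-up rate of 20%, 480 participants will be recruited in total".

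**The concern.** Three features act together.

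- A week-8 score replaced by baseline means zero change, so the patient is a non-responder with certainty, whatever was recorded at other visits. A patient who leaves before any post-baseline measurement drops out of the denominator instead. On the usual reading, the timing of withdrawal decides between exclusion and failure.
- The apparent response rate then mixes response with retention. If retention differs by arm, the primary comparison is biased, and the SAP rests its conclusions on the primary outcome.
- The three checks are meant to show robustness. None varies the assumption about unobserved outcomes separately by arm, and the multiple imputation as listed uses neither treatment arm nor any pain or function score.

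The risk is that the primary analysis and its checks share an error and their agreement is read as robustness.

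**Working it through.** **The plan's own figure.** Inputs: 60% vs 40%, two-sided 0.025 (z = 2.2414), power 80% (z = 0.8416).

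n = [2.2414·√(2·0.5·0.5) + 0.8416·√(0.6·0.4 + 0.4·0.6)]² / 0.20² = 117.5

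With continuity correction: (117.5/4)·[1 + √(1 + 4/(117.5·0.20))]² = 127.3, so 128 per group. Then 128/0.80 = 160 per arm and 3 × 160 = 480. Both stated figures reproduce. The calculation treats the 20% lost as removed, whereas the primary analysis keeps those it imputes as non-responders.

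**Model for the primary rule.** With true response p and a fraction m missing at week 8 regardless of outcome, apparent response = p·(1 − m). Rejection rates are exact binomial sums for the pooled Z-test at two-sided 0.025 with 160 per arm, unless stated otherwise. The SAP gives no drop-out by arm, so every split is an assumption. All missing patients are taken to be in the analysis set.

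**1. Equal drop-out, 20% in each arm, unrelated to outcome**
- No effect: apparent rates are equal (for example 0.40·0.80 = 32% in both arms) and rejection stays at 2.5%.
- MA vs SA: 0.60·0.80 = 48% against 0.40·0.80 = 32%. Power is 76%, compared with 85% for 128 completers per arm at 60% vs 40%.
- EA vs SA: 0.70·0.80 = 56% against 32%. Power is 98% (normal approximation).

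**2. Unequal drop-out, unrelated to outcome**

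| Truth | Missing, active / sham | Apparent rates | Primary rule rejects | Deletion rejects |
|---|---|---|---|---|
| 40% vs 40% | 10% / 25% | 36% vs 30% | 13.5% | 2.5% (144 vs 120 patients) |
| 40% vs 40% | 10% / 20% | 36% vs 32% | 6.9% | 2.6% (144 vs 128) |
| 60% vs 40% | 20% / 10% | 48% vs 36% | 48.5% | 85.9% (128 vs 144) |

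The bias favours whichever arm retains more patients. In all three rows deletion is free of it, so the two analyses would disagree visibly.

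**3. Missingness that depends on outcome, in opposite directions by arm.** True response is 50% in both arms, with 20% missing in each. In the active arm 10% of responders and 30% of non-responders are missing; in sham the reverse.
- Observed responders, active: 0.5·0.90 = 45% of those randomised. Sham: 0.5·0.70 = 35%.
- Primary rule: 45% vs 35%, a false difference of 10 points. False positives are about 34%.
- Deletion: 45/80 = 56.25% vs 35/80 = 43.75%, a false difference of 12.5 points. False positives are 43% with exactly 128 completers per arm, and about 40% when the number of completers varies at random.
- Multiple imputation without arm (five imputations, uninformative covariates): the missing take the pooled observed rate of 50%, giving 45 + 0.20·50 = 55% vs 35 + 0.20·50 = 45%. The difference is 10 points, with about 22% false positives in 20,000 simulated trials.

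With a milder 15%/25% split in place of 10%/30%, the three rates are about 9.8%, 11.1% and 4.4%, against a nominal 1.25% in that direction. Last observation carried forward was not evaluated, because the SAP gives no week-4 rates.

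**4. The imputation model as listed.** True 60% vs 40%, 20% missing in each arm, unrelated to outcome. Without arm, the missing take the pooled rate of 50%: 0.80·60 + 0.20·50 = 58% vs 0.80·40 + 0.20·50 = 42%. The 20-point difference becomes 16. Simulated power is about 65%, compared with 84% for deletion. This assumes that the five listed covariates carry no information on response.

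**The case against.** Counting missing responders as failures is a common, pre-specified rule, applied identically in all arms and backed by three alternatives. Its absence of a tipping-point analysis contradicts nothing in the document. This stands, and is why the primary rule need not change.

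A reader might infer that no sensitivity scheme lets missing outcomes differ by arm. That is too strong. Last observation carried forward uses each patient's own score, and deletion implicitly gives each arm its own observed rate. Only the imputation list leaves arm out, and an article may condense a fuller specification.

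A reader might also infer that the primary rule could produce a positive result that the plan would not detect. When drop-out is unrelated to outcome, deletion exposes it, and the SAP lists losses and reasons by arm. A case in which all active losses fall before week 4 and all sham losses after gives about 20.6% rejection at 40% true response and 20% loss. It is an all-or-nothing split, and deletion returns it to 2.6%. The SAP also does not say which post-baseline measurement counts; credibility and expectancy are recorded 5 minutes after the first session.

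Nor do the documents show that sham patients would leave more often. Patients are masked, and the absence of current cannot separate MA from SA. The direction of any imbalance is unknown.

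**Conclusion.** The point holds in a limited form. Baseline imputation makes these patients certain non-responders. Equal drop-out unrelated to outcome leaves the false-positive rate alone but costs power: about 76% for MA vs SA if all of the planned 20% loss is imputed, less of a cost if some leave before any measurement. Unequal drop-out biases the primary test in either direction, and deletion would show it.

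Two gaps remain. No planned analysis addresses missingness that depends on outcome differently by arm; in the assumed 10%/30% case, baseline imputation (about 34%), deletion (40 to 43%) and the listed imputation (about 22%) err together. And the imputation, as listed, pulls the arms together, to about 16 points from a true 20. The splits are illustrations, not forecasts, and lie at the upper end because the rule reaches only patients with a post-baseline measurement. The document does not support saying that the primary result will be spurious. This is a cheap improvement to the sensitivity analyses.

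**What to change.** Keep the primary rule and amend the additional analyses section.

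(a) Run the multiple imputation by arm, or include arm in the model, and add baseline, week-4 and later NRS and WOMAC function scores to the listed variables.

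(b) Add a delta-adjusted tipping-point analysis, varied separately by arm, for EA vs SA and for MA vs SA. Report the response rates among missing patients in each arm at which P crosses 0.025.

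Change (a) alone is not enough. Imputing by arm with uninformative covariates would reproduce the deletion result in step 3 (56.25% vs 43.75%), so (b) is what addresses that case.

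The cost is SAP wording and some added PROC MI code, with no new data. The downside is one more sensitivity table and a result that may look less robust.
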